#### Macroeconomic Trends and Health Factors

To evaluate historical trends in the relocation patterns of older adults, descriptive statistics will be used. Means will be described over time for different groups of individuals, depending on age and macroeconomic characteristics for the specific year of the relocations.

To analyze how health factors influence relocation, we will use descriptive and inferential statistics such as odds ratios, mean comparisons, and multivariate regression analyses.

### Focus Group Study

To explore how older homeowners reason about their current housing situation in relation to future needs and opportunities to move and what financial and health-related factors they perceive as important in such a decision-making process, data will be collected from a series of focus groups [34] in 4 municipalities across Sweden.

#### Selection of Municipalities and Recruitment of Participants

Four heterogeneous municipalities have been selected based on demographics (ie, proportion of older adults), local housing market structure (eg, range of housing types, price, rent levels, and new production of housing that matches the needs of older adults), and geographic location.

Participants will be recruited via senior citizens’ organizations [19] and through advertisements on social media. The selection of interested participants will be based on similarities dictated by the purpose of the study [34] and heterogeneity among them (eg, sex, age, and living situation) to explore various perspectives. A total of 64 people will be recruited into 8 groups (ie, 2 focus groups per municipality), with 8 participants in each.

#### Data Collection

The interview guide will be developed based on findings from the register study, theories underpinning the project, relevant literature, and current media discourse. The groups will meet twice each, and the preliminary results from the first sessions will be used to adapt the interview guide for the second session to allow deeper exploration of the themes that emerge. If a need to contrast different perspectives emerges in the analysis, the participant constellations may change during the second session. Two moderators will lead each group: one will lead the discussions, and one will observe group interactions and listen to the discussions [34]. Sessions will be audio-recorded and last approximately 2 hours. The observing moderator will take field notes on settings and group dynamics as well as pose clarifying questions. At the end of each session, the observing moderator will give a brief summary of the core issues discussed and allow participants to comment and suggest amendments.

#### Analyses

We will use a constant comparative analytic framework as described by Krueger and Casey [34]. After round 2, audiotapes will be transcribed verbatim. The moderators will read the transcripts and listen to the recordings to get a feel for the dynamics of the discussions and independently code the data. This includes identifying patterns in the data and relationships among concepts. NVivo (Lumivero) will be used as it promotes transparency and validation of coding. To further enhance trustworthiness and reduce potential bias, peer debriefing meetings with all coauthors will be held throughout the analysis process [35].

### Survey Study

#### Overview

The survey study will include a random sample of homeowners aged 55 years and older living across Sweden. In Sweden, approximately 3.71 million people are aged 50 years or older. Within this group, 2.8 million (70%) live in privately owned accommodations: 2.13 million in houses and 710,000 in condominiums [36]. Because men own their homes to a greater extent than women of older age, participants will be stratified by sex and randomly selected from the Swedish national population registry. Using a 95% CI and a margin of error of 4, we estimate a total sample size [37] of 3600 to be representative. We expect a 40%-50% response rate and will therefore draw an initial sample of 7200.

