### Study Objective and Research Questions

AGE-HERE aims to develop new knowledge on relationships between economic factors and health that incentivize or disincentivize relocation among homeowners from an early stage of the aging process (55 years and older). The specific research questions are as follows:

How did macroeconomic events during the period 1970-2016 affect relocation patterns across time for older homeowners of different ages? Are there different patterns of relocation depending on civil status and sex?In what way did the tax reform of 2008 affect the probability of moving among older homeowners?What economic factors predict relocation to different types of housing (eg, condominiums, owner-occupied housing, and rental apartments), taking health factors into account?What economic and health factors do older homeowners perceive as important when considering relocation?What are older homeowners’ preferences and beliefs regarding the economic factors that disincentivize or incentivize relocation?To what extent do older homeowners report that economic factors are an important part of the relocation decision process?How are economic factors and health related to decisions to move among older homeowners?How are the questions above affected by regional differences and housing market structures?

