#### Survey Data Collection Procedures

Results from the register study and focus group study will be used to develop the survey questions in an iterative process involving the nonacademic reference group. The reference group will provide input to ensure the survey length is reasonable, the questions and response choices are clear and understandable, and the items cover the content identified in the previous studies. Sociodemographic questions and established self-rating scales on quality of life, independence, participation, and health will be integrated into the survey to explore the relationships between personal factors, health, and economic factors in decisions to relocate. The survey will be tested in a pilot with a sample drawn from the target population for the main study (n=25), and questions and procedures will be modified based on the results.

A professional survey company will be contracted for the data collection [19]. Potential participants will be sent a postal invitation, which includes a detailed description of the study and instructions for how to opt out. Participants will be able to complete the survey via the internet, using a paper form, or via telephone. Those who have not completed a web-based survey or requested a paper survey after 2 weeks will be contacted by trained interviewers who can conduct the survey using a computer-assisted telephone interview protocol. Data collection will continue until the target sample size is reached.

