#### Analyses

Descriptive statistics will be used to analyze the demographics of each stratum and compare them with national population statistics. If results differ from the population, sample weights to match the population will be created. Weighted sample statistics will be used to describe the prevalence of reported economic incentives or disincentives, and a 2-tailed *t* test will be used to identify sex differences. Univariate and multivariate linear and logistic regression models will be used to assess associations between economic factors, health, and sociodemographic variables.

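### The survey target of 3600 does not follow from the stated 95% CI and margin of 4, which call for about 600 responses overall or about 1200 across the two sexes; the survey is more precise than stated

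*Protocol article*

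**What the plan says.** The size of the national survey is justified in one sentence of the protocol article (Methods, Survey Study, Overview): "Using a 95% CI and a margin of error of 4, we estimate a total sample size [37] of 3600 to be representative". The unit of the margin, the assumed proportion, any design effect and the group to which the margin applies are not given.

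The same paragraph names one stratification factor: "participants will be stratified by sex and randomly selected from the Swedish national population registry". It then allows for nonresponse: "We expect a 40%-50% response rate and will therefore draw an initial sample of 7200". Survey Data Collection Procedures adds: "Data collection will continue until the target sample size is reached". So 3600 is a count of completed surveys, not of invitations.

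The quantity to which a margin of error would naturally apply appears in the Analyses section of the Survey Study: "Weighted sample statistics will be used to describe the prevalence of reported economic incentives or disincentives". That is a proportion. The same section plans a comparison of the sexes, regression models, and weights if the strata differ from national statistics.

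**The concern.** The confidence level, the margin and the resulting size stand in one sentence, so a reader can check them against each other, and they disagree. The usual precision formula for a proportion gives about one sixth of the stated size for a single overall estimate, and about one third if the margin must hold in each sex.

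The stake is what readers take the survey's precision to be and whether its size can be justified. As printed, the sentence gives ±4 as the precision behind a sample that delivers something different, and it leaves the target of 3600, and so the draw of 7200, without a basis that reproduces. It also ties being representative to the number of respondents. Size governs sampling error. Whether respondents resemble the population depends on how they were drawn, who answers (50% to 60% are expected not to) and how the results are weighted.

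**Working it through.** **Inputs**
- Confidence 95%, two-sided, z = 1.96 (Survey Study, Overview).
- Margin 4, unit not stated; read here as e = 0.04, four percentage points either side (assumption).
- Proportion p not stated; p = 0.5 assumed, which gives the largest n. For comparison, p = 0.7 gives 505 and p = 0.2 gives 385.
- Population: 2.8 million owners aged 50 or older (same paragraph). The figure for 55 or older is not given, but at this order of magnitude the finite population correction is negligible.
- Completed target 3600; draw 7200; response 40% to 50%.
- Two sex strata; 1800 in each assumed, because the allocation is not stated.

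**Attempt to reproduce 3600**

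n = z² p(1−p) / e² = 1.96² × 0.25 / 0.04² = 0.9604 / 0.0016 = 600.25, so about 600 (600.1 with the finite population correction).

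±4 in each sex: 2 × 600.25 = 1200.5, so about 1200.

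Other readings of the same inputs:

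| Reading | Required n |
|---|---|
| One-sided 95% | 423 |
| Continuity correction | 626 |
| 99% CI, ±4 | 1037 |
| ±4 on the difference between the sexes (total) | 2401 |
| 4 as full interval width (±2) | 2401 |
| ±2 in each sex | 4802 |
| 99% CI, ±2 | 4147 |
| ±4 overall, inflated for 50% to 40% response | 1201 to 1501 |

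None is within 3% of 3600. The inflation row is shown only for completeness, since nonresponse is already handled by the step from 3600 to 7200 (3600 / 0.5 = 7200).

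**Routes that do reach 3600, each with an assumption the article does not state**
- ±4 in each of six groups: 6 × 600.25 = 3601.5.
- ±2 with a design effect of 1.5: 1.96² × 0.25 / 0.02² × 1.5 = 2401 × 1.5 = 3601.5.
- A relative margin of 4% at p = 0.4: 1.96² × 0.6 / (0.4 × 0.04²) = 2.30496 / 0.00064 = 3601.5.

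**Precision that the planned size delivers** (p = 0.5, no design effect)
- Overall, 3600: 1.96 × √(0.25/3600) = 0.0163, or ±1.6 points.
- Per sex, 1800: 1.96 × √(0.25/1800) = 0.0231, or ±2.3 points.
- Difference between the sexes: 1.96 × √(0.5/1800) = 0.0327, or ±3.3 points.
- At 40% response: 7200 × 0.4 = 2880, and 1.96 × √(0.25/2880) = 0.0183, or ±1.8 points overall.

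**Room for a weighting design effect.** The overall margin at 3600 would reach ±4 only with a design effect of 3600 / 600.25 ≈ 6.0; the per-sex margin only with 1800 / 600.25 ≈ 3.0.

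**The case against.** The strongest reply is that this is an incompletely specified calculation, not a proven arithmetic slip. The sentence cites a source for the sample size, and a journal article may leave the assumed proportion, the design effect or the subgroup requirement to a fuller document. Three different unstated assumptions each give about 3600. This stands as far as it goes: the cause of the mismatch cannot be determined from the article. It does not rescue the sentence, which presents 3600 as the result of two inputs that do not produce it.

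Second, no harm follows for the stated margin. Overall and per-sex estimates are more precise than ±4, and the overall margin stays well inside it at the lower response rate. That is correct and sets the size of the point. Nor is the larger sample shown to be wasteful, since the plan also compares the sexes and fits regression models.

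Third, the plan does not rest representativeness on size alone. It has a random registry draw, several response modes with telephone follow-up, a comparison with national statistics, and weights if needed. These do not remove nonresponse bias, but they reduce this part of the point to wording.

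A reader might go further and infer from the ratio of almost exactly six that ±4 was meant in each of six reporting groups, and that a draw stratified by sex alone fails to secure them. The research question "How are the questions above affected by regional differences and housing market structures" makes that tempting. The documents do not support it. No six groups are named, two other routes give the same number, and the regional question sets no margin per region and can be examined by regression.

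**Conclusion.** The point holds in a limited form. The stated inputs give about 600 completed responses overall, or about 1200 if the margin is to hold in each sex; 3600 is about six and three times these figures. The survey is not undersized for ±4. At 3600 it delivers about ±1.6 points overall and ±2.3 points per sex, and at 40% response about ±1.8 points overall.

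This rests on reading 4 as percentage points, on p = 0.5 (any other proportion makes the required number smaller and the gap larger), on an equal split by sex, and on no design effect. Weighting will widen the intervals somewhat, but the design effect would have to be about 6 overall, or 3 per sex, to bring them to ±4 at 3600. Whether the cause is a slip or an unstated assumption is open. What is established is that the number does not reproduce from its printed basis.

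**What to change.** Rewrite the sample-size sentence in one of two ways.

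1. Keep 3600 and state what it delivers: for a prevalence near 50%, a 95% CI half-width of about 1.6 points overall and 2.3 points in each sex with 1800 each, before any design effect from weighting, and about 1.8 points overall if response is 40% and the draw yields 2880.
2. If 3600 came from another basis (margins within subgroups, a design effect or a relative margin), state that basis in full, with the assumed proportion and the unit of the margin, so that the number reproduces.

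In either case, describe the size as setting precision, and attribute representativeness to the random draw from the registry and to the comparison and weighting already planned.

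The cost is one or two sentences. The target, the draw and the stratification by sex can stay as they are; nothing here calls for a new stratification.

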#### Survey Data Collection Procedures

Results from the register study and focus group study will be used to develop the survey questions in an iterative process involving the nonacademic reference group. The reference group will provide input to ensure the survey length is reasonable, the questions and response choices are clear and understandable, and the items cover the content identified in the previous studies. Sociodemographic questions and established self-rating scales on quality of life, independence, participation, and health will be integrated into the survey to explore the relationships between personal factors, health, and economic factors in decisions to relocate. The survey will be tested in a pilot with a sample drawn from the target population for the main study (n=25), and questions and procedures will be modified based on the results.

A professional survey company will be contracted for the data collection [19]. Potential participants will be sent a postal invitation, which includes a detailed description of the study and instructions for how to opt out. Participants will be able to complete the survey via the internet, using a paper form, or via telephone. Those who have not completed a web-based survey or requested a paper survey after 2 weeks will be contacted by trained interviewers who can conduct the survey using a computer-assisted telephone interview protocol. Data collection will continue until the target sample size is reached.

#### Analyses

Descriptive statistics will be used to analyze the demographics of each stratum and compare them with national population statistics. If results differ from the population, sample weights to match the population will be created. Weighted sample statistics will be used to describe the prevalence of reported economic incentives or disincentives, and a 2-tailed *t* test will be used to identify sex differences. Univariate and multivariate linear and logistic regression models will be used to assess associations between economic factors, health, and sociodemographic variables.

### Integration Study

As a final step, toward the end of the project (in 2025), the results will be merged and interpreted as a whole [31]. The purposes are triangulation (ie, validation based on corroboration between data sets), complementarity (ie, different methods to answer related questions), and expansion (ie, data sources address different aspects of answering questions raised by other data sets) [38,39]. Using an interactive merging strategy, narrative integration and weaving, presenting qualitative and quantitative data together, and forming connections based on specific topics will be used [40]. Analysis meetings involving the reference group will be an integral part. Emerging themes will be explored and developed based on Roy et al’s [4] framework, the theoretical underpinnings, relevant international or national reports, policy documents, and legislation.

### Ethics Approval

Ethical approval for the register study (DNR 2022-04626-01) and focus group study (DNR 2023-01887-01) has been obtained from the Swedish Ethical Review Authority. We will adhere strictly to the Helsinki Declaration’s requirements for research involving humans. Because a systematic examination of ethical considerations is also needed in the survey study, an additional ethical approval will be sought. We will make sure that project staff are trained and supervised on ethical issues, with specific attention to collecting data from older adults. In case participants have questions, contact information of the responsible researchers will be provided for the focus group study and the survey study. In the information letter to study participants, they will be informed about confidentiality and their right to withdraw from the study at any time. Informed consent will be obtained first after the participants have been given written and oral information on the study’s purpose and what participation would entail. All data will be collected and stored in compliance with the requirements of the Ethical Review Authority and the European General Data Protection Regulation.

## Results

Ethical approval for the register study and focus group study has been obtained (DNR 2022-04626-01, DNR 2023-01887-01 respectively). Data analyses (register study) and data collection (focus group study) are currently being conducted (July 2023). The first paper based on the register data is expected to be submitted during the summer of 2023. Three meetings have been held with the nonacademic reference group. The qualitative data will be analyzed in the autumn. Based on the results of these studies, a survey questionnaire will be developed and distributed nationally during the spring of 2024, followed by data analyses in the autumn. Finally, the results from all studies will be synthesized in 2025.

## Discussion

### Principal Findings

This project sets out to investigate how economic and health aspects influence the decision to relocate or not among older adults. By integrating theory and methods from economics and gerontology, we will identify the most influential factors in older homeowners’ housing decisions. We expect that economic policies play an important role in the decision to remain in single-family homes even when the home no longer supports older adults with declining health. Furthermore, we expect this decision to also be related to a lack of affordable housing with good accessibility in the Swedish housing market. Although we specifically focus on Sweden, the project has broader geographical implications. Hence, findings can be used to inform the allocation of resources and policy decisions concerning the living arrangements and housing choices of older adults in countries where comparable housing policies are being implemented or intended.

Aging in place has become the norm for most older adults in Sweden as well as in other Western countries, which is supported by society as it is considered less costly to provide home care than care in institutions [41]. Even so, most research on housing and aging does not consider factors that incentivize or disincentivize relocation within the ordinary housing stock; instead, the focus is on people aging with disabilities or frailty, with growing needs for special forms of housing and housing adaptations [14]. Given that aging in place is far from supportive for all older adults [42], future research and policy initiatives should focus on the diverse needs of the heterogeneous aging population [43] and consider aging in the right place [44]. This is important because, with population aging, the share of older adults living with functional limitations and age-related diseases will increase [45], implying that the housing stock needs to be adapted and developed to fit the needs and preferences of this substantial population segment. The dwellings older homeowners tend to live in often have a high prevalence of environmental barriers, and older adults aging with functional limitations experience accessibility problems, which can hinder daily activities and have negative consequences for health and quality of life [9,46,47]. From a societal economic and public health perspective, it is therefore important that municipalities comply with their housing provision responsibility and create conditions for everyone to be able to live in adequate housing [48].

Most older adults in Sweden live in dwellings they purchased much earlier in their lives and are now reticent about selling [49]. This trend is similar to the majority of OECD countries [25]. For example, in the United States, homeownership rates remain unchanged after the age of 55 years [50], and this trend has been relatively stable despite the economic recession and the housing market crash in 2007 [44]. The reluctance to sell contradicts the life cycle hypothesis, which says that older homeowners would sell their property in favor of renting or moving to a smaller, less costly home to start “consuming” or using their equity to support their living costs [50]. While many factors can explain why older homeowners are reluctant to move (eg, attachment to a place), concerns about the associated costs have gained little attention. This has been highlighted by Sweden’s largest senior organization, showing that every fifth senior household in Sweden has decided not to move because of the capital gains tax [49]. This means that a substantial number of moves do not happen, which in turn slows down relocation chains and reduces the housing supply for young families who are in need of a larger home.

While there are other recent reports highlighting this issue [51], no scientific efforts have so far been made in Sweden or internationally to understand this complexity in depth. Overall, there is a paucity of studies investigating associations between taxation and decisions to move. Previous studies are based on US conditions and aggregated data [52], where the property tax is local and used to finance local public services and therefore affects the choice to move. As such, the AGE-HERE register study represents a novel approach compared to existing research, as we will study the impact of taxes on housing decisions in older age using high-quality register data. The design of the Swedish property tax, which is national rather than local (and therefore does not interfere with the choice to move), allows us to test this empirically in a valid way. By linking registers with data on taxes, income, and health and using a framework based on a systematic literature review [28], we will be able to analyze a large range of factors. Adding to this, we will observe the number of relocations among older adults historically, which will provide unique knowledge on housing decisions depending on the state of the economy across time.

Turning to the focus group study, previous research conducted in 6 European countries (the United Kingdom, Germany, the Netherlands, Ireland, Italy, and Hungary) has shown that housing choices among older homeowners are highly dependent on the local housing market situation [53], which is seldom considered in research. Our approach in AGE-HERE to collect data in 4 different municipalities across Sweden will provide valuable insights related not only to the range of possible factors that influence older homeowners’ decisions to move but also to the role played by preconditions in local housing markets. Local housing markets are heterogeneous and need to be considered by housing policymakers. For example, in some municipalities, almost the entire housing stock consists of single-family houses, which limits the possibility of moving to a smaller dwelling when needs and preconditions change. In contrast, other municipalities have a large variety of smaller dwellings, both rentals and condominiums. In terms of new production, especially forms of housing that are aimed at the older population, some municipalities have many completed and ongoing projects while others have few. It is not farfetched to believe that such diverse situations will be a huge challenge in the coming years as the share of older people will increase substantially in all municipalities. That is, housing needs will change with population aging, and therefore policymakers need to relate to this diversity of prerequisites when planning for the future.

By better understanding the living conditions of older people from their own diverse perspectives, we can promote a positive development of social relations and enhance full participation in society on an individual level. Additionally, a better functioning housing market would have positive spillover effects on the labor market because relocation chains would function better and on the financial markets because real estate prices would be adjusted, which in turn would affect households’ debt levels [3]. Altogether, a better-functioning housing market will enhance not only health and well-being but also the economic performance of society.

